# 1 Introduction

## 1.1 Background

The effect of Cardiac Resynchronization Therapy (CRT) on Chronic Heart Failure (CHF) has been recognized internationally. The multi-center clinical study proved that CRT could not only improve the cardiac function of CHF patients with CHF with cardiac dyssynchrony, increase 6-Minute Hall Walk Distance (6MHWd), improve quality of life, reduce admission rate and reverse LV remodeling, but also significantly reduce mortality of HF patients and improve their clinical prognosis. Therefore, the heart failure treatment guidelines developed by European Society of Cardiology (ESC) and American College of Cardiology/American Heart Association (ACC/AHA) in 2005 changed the indications for CRT device implantation from Class IIa to Class I in some CHF patients with cardiac dyssynchrony in succession.

## 1.2 Interval Optimization

The purpose of this CRT is to reduce even eliminate the AV, VV and intraventricular systolic dyssynchrony through providing appropriate AV interval and VV interval so as to improve the hemodynamic status of CHF patients. The optimization of AV interval improves the effective LV filling in CRT patients while the purpose of the optimization of VV interval is to weaken LV dyssynchrony and reduce mitral regurgitation and improve some non-responders with only AV interval optimized to responders. Therefore, the importance of optimization of AV and VV intervals on the improvement of clinical efficacy in CRT patients has been recognized.

Currently, the commonly used optimization method is echocardiography; however, since the echocardiographic optimization is expensive, time-consuming and with low reproducibility, many patients receive interval optimization only before they are discharged or when they have poor response to CRT so that the clinical efficacy of CRT is adversely affected. In addition, the optimal value of AV interval in patients receiving CRT changes with the time. As a result, the AV interval shall be optimized periodically based on the change of conditions in clinical practice to improve the clinical efficacy of CRT.

According to the epidemiology and current indications for CRT device implantation, there are approximately 300,000 CHF patients requiring CRT-P/D implantation in China. In 2009, the total number of implanted CRT-P/Ds was more than 1,000 in China with significant increase trend in annual quantity. Therefore, the post-implantation parameter optimization has become a great challenge in clinical practice.

QuickOpt™ developed by St Medical (SJM) in 2007 provides a rapid interval optimization using intracardiac ECG. That is to say during routine follow-up using programmer, for the optimized AV interval and VV interval calculated according to specific sensing and pacemaker intracardiac ECG, the purpose of AV interval optimization is to try to maximize the ventricular preload and close the mitral valve at appropriate time while the purpose of VV interval optimization is to try to make the wave fronts activated at LV and RV leads meet near interventricular septum, so as to reduce cardiac dyssynchrony.

In comparison with echocardiographic optimization, interval optimization with QuickOpt™ is time saving and economical with good patient compliance. The currently published clinical study results demonstrated that the aortic velocity time integral (AVTI) obtained through QuickOpt™ optimization was significantly associated with the maximum AVTI through echocardiographic

optimization, with the correlation coefficient up to 0.96-0.98. In addition, both QuickOpt™ optimization and echocardiographic optimization improve the hemodynamics in heart failure patients. The study showed that compared with the real-time three-dimensional echocardiography (RT3DE) method, the LV synchronization and clinical manifestations of patients before and after interval optimization were significantly improved with the QuickOpt™ interval optimization.

Nonetheless, the effect of QuickOpt™ interval optimization on the patients' middle- and long-term clinical efficacy remains unclear. To provide reference to the clinicians engaged in CRT-P/D interval optimization, it is proposed to conduct a randomized, double-blind, multicenter and parallel control study in China to observe the effect of QuickOpt™ optimization method on the efficacy in patients at one year post-CRT-P/D implantation compared with echocardiographic optimization. Moreover, the clinical improvement of CRT-P/D patients after standard and regular optimization will be assessed.

### **1.3 Left ventricular (LV) remodeling**

Biventricular pacing could improve the LV remodeling, including the change of LV end-systolic volume (LVESV) and LV end-diastolic volume (LVEDV). The MIRACLE study demonstrated that the indicators of cardiac remodeling were significantly improved one year after CRT-D implantation. In addition, the improvement of LVESV was closely associated with the clinical outcome. Therefore, the decrease in LVESV is often used as an important outcome measure to evaluate whether the patients respond to CRT or not.

For that reason, this study takes cardiac remodeling status as the primary endpoint and LVESV as the outcome measure.

### **1.4 Assessment of body function**

Specific Activity Scale (SAS) is a simple method to assess the body function status, which is to grade the exercise capacity in metabolic equivalents (METs) of each individual instead of a simple assessment of quality of life. SAS has been used for the clinical trials conducted in regions that are different in cultures and languages, including many studies in North America, Australia, New Zealand, Greece, Sweden, Denmark, Spain and Japan so as to assess the treatment response of HF patients. In this study, SAS is used as an outcome measure for body function assessment.

6-Minute Hall Walk Distance (6MHWd) is an outcome measure to detect the exercise tolerance of individuals. In 1985, the study by Guyatt found that 6 MHWd had strong stability and good reproducibility in the evaluation of heart function in CHF patients. Since then there were multiple clinical studies on CHF that evaluated the heart function using 6 MHWd. In the CHF diagnosis and treatment guidelines issued by ACC/AHA in 2002 and 2005, 6-MHWd was specified as a measure for heart function assessment. 6-MHWd has become a common index for the evaluation of heart function of CHF patients now and is generally used for the evaluation of symptom improvement of cardiac function with CRT. It is widely used in multiple studies in the world at present.

## **2 Study objectives**

### **2.1 Purpose**

#### **2.1.1 Primary objectives**

To demonstrate whether QuickOpt™ can be used as an alternative CRT-P/D optimization method in clinical practice through the comparison of QuickOpt™ optimization with echocardiographic optimization in the clinical improvement in patients at 12 months after CRT-P/D implantation.

- (1) To assess the improvement of LV remodeling (LVESV) through QuickOpt™ optimization and echocardiographic optimization in HF patients at 12 months after CRT-P/D implantation.
- (2) To assess the change of other clinical manifestations (NYHA class, SAS and 6-MHWD) in above patients with above two different optimization methods.

#### **2.1.2 Secondary objective**

To investigate the overall clinical efficacy of CRT-P/D patients receiving regular standard optimization under current medical environment in Mainland China through assessing the clinical improvement in included patients at 12 months after CRT-P/D implantation.

### **2.2 Study endpoints**

#### **2.2.1 Primary endpoint**

Cardiac remodeling indicator at 12 months after implantation: LVESV

To minimize the disadvantages of poor reproducibility and large accidental error for echocardiographic measurement, the enrolled patients in each site will be performed with echocardiography by the Echocardiographic Core Laboratory for uniform measurement in this study.

#### **2.2.2 Secondary endpoints**

Clinical outcome measures at 12 months after implantation: NYHA class

SAS

6- MHWD

To minimize the effect of the investigators' subjective factors during the assessment of above items, the assessment of these items will be completed by the blinded investigator who will not be informed of the specific optimization method of the patients.

#### **2.2.3 Additional data**

Other echocardiographic indexes at 12 months after implantation: LVEF

Mitral regurgitation area

Diagnostic data by programmer: atrium: atrial pacing percentage (%)

AT /AF burden

Times of auto mode switch (AMS)

Ventricle: ventricular pacing percentage (%)

ventricular arrhythmia

Comparison of time consumption between two optimization methods

Drug therapy

Clinical event: emergency, hospitalization, death, etc.

## **2.3 Screening criteria of patients**

### **2.3.1 Inclusion criteria**

The patients can be included into the study only when they meet all the inclusion criteria below:

- Patients with the indications for the implantation of CRT and CRT-P/D who have been implanted with complete lead system (RA lead, RV lead and LV lead) manufactured by SJM
- Able to and willing to receive the regular follow-up as required by this study
- Suitable for drug therapy as appropriate.

### **2.3.2 Exclusion criteria**

The patients who meet any of the following exclusion criteria shall not participate in the study:

- Severe sinus bradycardia (sinus rate  $\leq$  40bpm)
- Persistent and chronic rapid atrial arrhythmia, including atrial fibrillation, atrial flutter, atrial tachycardia
- II or III degree AV block
- Life expectancy < 1 year
- Age < 18 years
- Pregnant and lactating women
- Patients on the treatment of IV positive inotropic drugs
- Patients who are participating in the study of other devices or drugs
- Patients who underwent or plan to undergo heart transplantation
- Hypertrophic obstructive cardiomyopathy
- Patients with severe aortic or mitral stenosis or insufficiency and have not undergone valve replacement
- Patients who underwent coronary artery bypass grafting, percutaneous coronary intervention or cardiomyoplasty within six weeks before inclusion or those with acute coronary syndrome or stroke.
- Patients with pre-excitation syndrome

## **2.4 Study design**

This is a prospective, randomized, double-blind, multicenter (Mainland China), parallel control, non-inferiority, and postmarketing study. The patients who were implanted with CRT-P or CRT-D are randomized to QuickOpt™ optimization group or echocardiographic optimization group in a

1:1 ratio within two weeks after implantation, and followed-up at 3 ( $\pm 2$  weeks), 6 ( $\pm 2$  weeks), and 12 ( $\pm 2$  weeks) months after implantation. In addition to 12 months after implantation, the patients will undergo interval optimization with corresponding method at enrollment, 3 and 6 months, and the optimal AV interval obtained by the optimization are programmed to the patients' CRT-P/D; it is necessary to determine and collect the clinical data at each follow-up.

## 2.4.1 Study Procedures

[figure not shown]

### Note:

Unscheduled follow up: In case of any unscheduled follow up for any reason and change of pacing parameters or drug therapy, it is required to fill the unscheduled follow up CRF.

All follow-ups: The optimization results of patients in each group should be used. Otherwise, it is necessary to complete the protocol deviation form and corresponding assessment should be performed. This patient will be followed-up as per the study protocol and included in "intent-to-treat analysis" population for analysis.

**Table 1: Data Collection**

| Tested by                                                                          | Item                                                                                                   | Enrollment                     | 3 months    | 6 months    | 12 months   | Unscheduled follow up          |
|------------------------------------------------------------------------------------|--------------------------------------------------------------------------------------------------------|--------------------------------|-------------|-------------|-------------|--------------------------------|
|                                                                                    |                                                                                                        | Within 2 weeks after operation | (± 2 weeks) | (± 2 weeks) | (± 2 weeks) | Unscheduled                    |
| Sampling: Echocardiography technician in each site
Measurement: core laboratory | Echocardiogram (DICOM format)                                                                          | √                              |             |             | √           |                                |
| Blinded investigator                                                               | NYHA class                                                                                             | √                              | √           | √           | √           | √                              |
|                                                                                    | SAS                                                                                                    | √                              |             |             | √           |                                |
|                                                                                    | 6 MHWd                                                                                                 | √                              |             |             | √           |                                |
| Investigator not blind to treatment                                                | 12-lead ECG                                                                                            | Non-pacing & pacing            | Pacing      | Pacing      | Pacing      | Non-pacing & pacing            |
|                                                                                    | Chest X-ray image (PA+LAO 45°)                                                                         |  √     |             |             |             |                                |
|                                                                                    | Clinical event*                                                                                        |                                | √           | √           | √           | √                              |
|                                                                                    | Pacemaker follow-up**:
Printing and retention of the follow-up data
Zeroing out: diagnostic data | √***                           | √           | √           | √           | Diagnostic data not zeroed out |
|                                                                                    | Interval Optimization                                                                                  | √                              | √           | √           |             | ****                           |
|                                                                                    | Drug therapy                                                                                           | √                              | √           | √           | √           | √                              |

**Note:** \*: Emergency, hospitalization, death event, etc. It is necessary to complete corresponding case report form

\*\* : Printing: diagnostic data, programmer test results, final programmed parameters  
For QuickOpt™ group, it is necessary to print the test results obtained from QuickOpt™

Storage: CRT-P stores the PDF document of above print contents  
CRT-D stores Session Record

\*\*\*: Program the diagnostic criteria for atrial and ventricular arrhythmia (determined by the investigator based on the clinical conditions) and open AMS  
For CRT-P, it is necessary to open the EGM Storage in trigger chamber for rapid ventricular rate

\*\*\*\*: The parameters can be adjusted based on the optimization results of different groups.

## 2.5 Devices used

### 2.5.1 CRT-P:

Frontier II 5596

### **2.5.2 CRT-D:**

|                   |                   |
|-------------------|-------------------|
| Epic +HF V350     | Atlas +HF V341    |
| Atlas II HF V365  | Atlas II+ HF V366 |
| Atlas II+ HF V367 | Promote 3107-30   |
| Promote 3107-36   |                   |

## **2.6 *Sample size and duration of the study***

The sample size is 400 including 260 for CRT-P and 140 for CRT-D.

The planned enrollment time is from Q1 in 2010 to December 31, 2011, followed by 1-year follow up and the whole study will be completed in December 2012. There are approximately 40 study sites in Mainland China participating in this study and at least ten patients are estimated to be enrolled in each site.

## 3 Protocol Description

### 3.1 Enrollment

The patients should sign the informed consent form before the study.

- The patients who meet all inclusion criteria and do not meet any exclusion criteria can be included.
- The patients who do not meet any inclusion criteria or meet any exclusion criteria cannot be included.

### 3.2 Baseline visit (within two weeks after implantation)

The enrolled patients are randomized to two groups within two weeks after implantation and, meanwhile, the investigator collects the baseline clinical data.

#### 3.2.1 Randomization

The CRT-P patients are randomized to QuickOpt™ optimization group or echocardiographic optimization group in a 1:1 ratio as per the randomized table with sample size of 260.

The CRT-D patients are randomized to QuickOpt™ optimization group or echocardiographic optimization group in a 1:1 ratio as per the randomized table with sample size of 140.

- QuickOpt™ optimization group: The patients' pacemaker is programmed according to the results of QuickOpt™ optimization (optimized sensing AV interval, optimized pacing AV interval and optimized VV interval). Time of follow-up requiring optimization: baseline (within two weeks after implantation), 3 ( $\pm 2$  weeks) months and 6 ( $\pm 2$  weeks) months; in addition, the investigator should determine whether to optimize interval at unscheduled follow-up.
- Echocardiographic optimization group: The patients' pacemaker is programmed according to the results of echocardiographic optimization (optimized sensing AV interval, optimized pacing AV interval and optimized VV interval). The same as QuickOpt™ optimization group for others. No specific requirement for specific method of echocardiographic optimization is set in this study and the method is determined by each site. The optimization sequence is from AV/PV interval to VV interval based on optimized PV interval. Please refer to the Appendix.

In this study, the patients will not be informed of the randomization to QuickOpt™ or echocardiographic optimization group.

#### 3.2.2 Baseline visit (within two weeks after implantation)

(1) Items in the charge of the clinical investigator:

##### ① Clinical Data

- Basic information of the patients
- 12-lead ECG (non-pacing & pacing)
- Chest X-ray (**PA+LAO 45°**)
- Information on pacing system implantation
- Pacemaker follow-up: the diagnostic criteria for atrial and ventricular arrhythmia (at

discretion of the investigator) will be programmed and AMS opened

- For CRT-P, it is necessary to open the EGM Storage in trigger chamber for rapid ventricular rate

Printing: diagnostic data, programmer test results, final programmed parameters

For QuickOpt™ group, it is necessary to print the QuickOpt™ test results

Storage: CRT-P stores the PDF of print contents.

CRT-D stores Session Record

- Zeroing out: diagnostic data zeroed out after printing and storage
- ② Optimization: optimize AV interval according to randomized group and program the optimization results to the pacemaker. If it fails to program based on the optimization results, it is necessary to complete the “protocol deviation form”.

Note: If the result of echocardiographic optimization is RV pacing first, to obtain appropriate left AV interval, the result of subtracting the optimized VV interval value from the optimized AV/PV interval is used as the AV/PV interval value for programming. Similarly, for current QuickOpt™, the optimization algorithm is to optimize AV interval and VV interval. Therefore, after QuickOpt™ optimization, if the result is RV pacing first, to obtain appropriate left AV interval, the result of subtracting the optimized VV interval value from the optimized AV/PV interval should be used as the AV/PV interval value for programming.

- Drug therapy

(2) Items in the charge of the blinded investigator:

NYHA class

SAS (refer to the appendix)

6-MHWD (refer to the appendix)

(3) Items in the charge of the echocardiography technician :

- Echocardiogram (stored in the disk in DICOM form to deliver to the core echocardiography laboratory for measurement)

### **3.3 3 & 6-month follow up after implantation**

(1) Time-window:  $\pm 2$  weeks

(2) Data collection: 12-lead ECG(pacing)

NYHA class (blinding)

Clinical event: emergency, hospitalization, death, etc.

Pacemaker follow-up: the same as the baseline

Change of drug therapy

(3) Optimization: optimize AV interval optimization according to randomized group and program the optimization results to the pacemaker.

QuickOpt™ optimization group: use QuickOpt™ to optimize and obtain the optimization results.

Echocardiographic optimization group: perform echocardiography to optimize and obtain the optimization results.

### **3.4 12-month follow up after implantation**

- (1) Time-window:  $\pm 2$  weeks
- (2) Clinical data: echocardiogram data, SAS and 6-MWHD , other data is same as 3 month follow up
- (3) Optimization: not required

### **3.5 Unscheduled follow up**

- (1) Time window: unscheduled
- (2) Clinical data: the same as three months. There is no need to zero out the diagnostic data of the programmer
- (3) Optimization: not required. If clinically indicated, it is necessary to optimize according to the randomized group

Note: In case of unscheduled follow up for any reason and change of pacing parameters or drug therapy, it is required to fill the unscheduled follow up CRF.

### **3.6 Deviation from protocol**

The investigator shall comply with the study plan, signed investigator agreement, applicable national or local laws or regulations, and related requirements or provisions of Ethics Committee and CFDA.

Deviation from study protocol refers to a condition where the actual situation is noncompliant with the study plan. The investigator shall inform SJM of any deviation that occurs within 5 working days as soon as possible to avoid threatening the life or health of patients.

### **3.7 Adverse events**

Any adverse medical event occurring from signing the informed consent form by the patients to the end of the study, regardless causal relationship between it and the investigational device, is considered adverse event (AE). Serious adverse event (SAE) refers to any adverse event leads to hospitalization and prolongation of the hospitalization, disability, influence on work capacity, is life-threatening or results in death during clinical study.

According to relevant guidelines in GCP, the investigator is responsible for making medical decisions on the relationship of the event and the clinical study to ensure that the subjects can be appropriately treated in case of any AE during study.

If the AE has no effect on the continuation of study, after the investigator provides appropriate treatment to the subjects, the subjects should continue to receive study treatment until the study is completed except that the subjects withdraw from the study.

The investigator shall classify and report all AEs related to the study protocol according to the severity of AE. All the serious adverse events shall be notified to the CRO by phone as soon as possible (within 24 hours) after awareness and reported to the principal investigator, SJM and relevant Ethics Committee by the CRO. In case of death, the complete follow-up report shall be printed. The common adverse event shall be reported to the CRO within five workdays and the adverse event form shall be completed.

AEs possibly related to CRT-P/D include, but not limited to:

- Hematoma
- Pneumothorax
- Hemothorax
- Venous thrombus
- Coronary sinus dissection
- Coronary sinus perforation
- Cardiac perforation
- Pericardial tamponade
- Infection
- Exposed pacing system
- Breathing or heartbeat pause
- Apnea
- Heartbeat pause
- Heart failure (deterioration)
- Myocardial infarction
- Chest wall stimulation
- Phrenic nerve or diaphragmatic stimulation
- Lead displacement or dislodgement
- Lead fracture

Lead insulation damage  
Increased pacing threshold  
Inadequate sensing  
Oversensing  
Premature battery depletion

Difficulties in programming or inability to communicate or program the pacemaker (i.e. implantation depth, electromagnetic interference or unknown cause)

Pulse generator fault is suspected

Others: all AEs not listed are classified as unexpected events. If the pacemaker, pacing lead system or delivery system causes any AE, SJM will report according to the post-market AE SOP.

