## **5 Risk and Benefit**

### **5.1 Risk**

The conventional treatment is performed in the whole study, and the diagnosis and treatment regimen is not changed as a result of the study. In case of any danger, the danger is caused by the conventional treatment instead of the study.

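### Section 3.7 contradicts itself on whether non-serious AEs are reported regardless of relatedness, and its SAE definition joins hospitalization and prolongation with *and*

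*Protocol*

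**What the plan says.** Protocol section 3.7 starts from a broad definition. Any untoward medical event between consent and the end of the study, "regardless causal relationship between it and the investigational device, is considered adverse event (AE").

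The duty to report is then put more narrowly: "The investigator shall classify and report all AEs related to the study protocol according to the severity of AE". Two specific rules follow directly:

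- for serious events, "All the serious adverse events shall be notified to the CRO by phone as soon as possible (within 24 hours) after awareness";
- for the rest, "The common adverse event shall be reported to the CRO within five workdays and the adverse event form shall be completed".

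On causality, "the investigator is responsible for making medical decisions on the relationship of the event and the clinical study"; the stated aim is that subjects receive proper treatment.

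An event is serious if, among other criteria, it "leads to hospitalization and prolongation of the hospitalization".

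Section 5.1 says that treatment is conventional throughout and unaltered by the study, and adds: "In case of any danger, the danger is caused by the conventional treatment instead of the study".

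A second route exists for major events. Section 3.3 lists among the data to collect: "Clinical event: emergency, hospitalization, death, etc". Table 1 extends this to the 12-month and unscheduled visits and places it with the investigator who is not blind to treatment.

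**The concern.** A site needs one answer to one question: does a non-serious event that the investigator considers unrelated go on an AE form? The definition and the five-workday rule point to yes. The general reporting sentence points to no, or at least gives grounds for no. Different sites can follow different sentences and each be compliant.

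The SAE definition raises a separate problem. A literal reader would not treat a new admission as serious unless the stay was also prolonged or another criterion applied, so the expedited notice would not be triggered.

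What is at stake is how complete and how prompt the safety record is. If relatedness is used to decide what is reported, the decision may be made by someone who knows the arm, because Table 1 gives both interval optimization and clinical-event recording to the unblinded investigator. Omissions could then differ by site and possibly by arm. Section 5.1 makes a relatedness test harder to apply, because it attributes any danger to routine care in advance.

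**Working it through.** No arithmetic applies. The check sets the sentences side by side and runs test cases through them.

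**1. Scope of each sentence in section 3.7**

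| Sentence | Events covered | Relatedness condition |
|---|---|---|
| AE definition | all, from consent to study end | none; causality to the device is set aside |
| General reporting duty | AEs tied to the study protocol | yes, undefined |
| SAE rule | all SAEs, within 24 hours | none |
| Common-AE rule | non-serious AEs, five workdays, AE form | none stated |

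Three of the four carry no condition and one does. Nothing says which governs, or whether the common-AE rule inherits the condition of the sentence that introduces it.

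**2. What relatedness refers to.** The section uses three referents: the investigational device (definition), the clinical study (investigator's judgement) and the study protocol (reporting duty). They are not the same. An event can be caused by the device and not by any study procedure.

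**3. Test cases for non-serious events**

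- *An event unrelated to device or study.* Reportable under the definition and the five-workday rule; not reportable under the general duty read literally.
- *A non-serious lead displacement or phrenic nerve stimulation.* Section 3.7 lists both as possibly related to the CRT device. They would usually be put down to the implant or device, and patients are randomised only after implantation (sections 2.4 and 3.2). Read literally, the general duty could leave them out. The list suggests that broad capture was intended, so the qualifier does not fit its own section.

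**4. Test case for the SAE definition.** Take a new admission of ordinary length that is not life-threatening, disabling or fatal and does not affect work capacity.

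- With *and*: admission is met, prolongation is not, so the criterion fails and the 24-hour notice is not literally due.
- With *or*: admission alone meets the criterion and the notice is due.

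Under *and*, the admission still appears as a clinical event at the next scheduled or unscheduled visit, and it falls under the five-workday rule if the site treats it as a common AE. It is late for expedited notice, not lost.

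**5. Section 5.1 against the design.** Section 5.1 says treatment is unaltered by the study. Sections 2.4 and 3.2.1 assign the optimization method at random and repeat it at baseline, 3 months and 6 months. Section 1.2 reports that in practice many patients are optimized only before discharge or when they respond poorly. By the protocol's own account, the study changes both how the method is chosen and, for many patients, how often it is applied.

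**6. Who applies the test.** Table 1 places clinical events and interval optimization with the unblinded investigator. Section 3.7 says only that the investigator reports AEs, without saying which one.

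**The case against.** The best defence is that section 3.7, read as a whole, works. The two specific rules come straight after the disputed sentence and set no relatedness condition. Together they cover serious and non-serious events, and a specific rule normally overrides a general one. The qualifier may be loose wording for events arising during the study. It also differs in subject from the definition, which speaks of the device and not the protocol, so the two are not strict opposites. The relationship judgement is there to guide treatment, not to select events. The SAE wording is probably a slip, and admissions are captured elsewhere. As for 5.1, this is a postmarketing study and both methods may be regarded as routine care.

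Much of this stands. It rules out three stronger readings that a reader might infer.

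- *That AE reporting is limited to related events.* It is not: SAEs and common AEs each have a rule without that condition.
- *That non-serious reporting could properly fall to none.* This would mean ignoring the five-workday sentence and treating 5.1 as a reporting rule. Section 5.1 is a risk statement, and 3.7 does not refer to it.
- *That a planned safety comparison is undermined.* The protocol defines none. The case for QuickOpt as an alternative rests on LVESV, NYHA class, SAS and walk distance (sections 2.1.1 and 2.2), and clinical events are additional data (section 2.2.3).

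The defence does not remove the contradiction. Whether the five-workday rule inherits the qualifier is exactly what the text leaves open. Capture as a clinical event does not carry the 24-hour clock. Calling the methods routine does not make their random allocation and fixed schedule routine.

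**Conclusion.** The point holds as an internal inconsistency in wording, in three parts:

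1. Section 3.7 does not settle whether non-serious AEs are reported regardless of relatedness.
2. Its SAE definition, taken literally, leaves a new admission alone outside the 24-hour notice.
3. The statement in 5.1 that treatment is unaltered conflicts with randomised, scheduled optimization.

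The size cannot be expressed as a number from the protocol. The first part is confined to non-serious events; the second concerns the timing of notice, not whether the admission is ever recorded. Sample size, primary endpoint and primary analysis are unaffected.

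The conclusion assumes that some sites would follow the reporting sentence literally. That omissions might differ by arm is an inference from who holds the tasks in Table 1; the protocol does not state it. How AEs are tabulated can be left to the SAP and is not part of this point.

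**What to change.** - **Section 3.7, reporting duty:** strike the words that tie reportable AEs to the study protocol, so that all AEs from consent to the end of the study are reported. Record relationship as a separate field on the AE form, and name its referent (device, study procedure, or both).
- **Section 3.7, SAE definition:** change *and* to *or* between hospitalization and its prolongation.
- **Section 5.1:** reconcile the statements on unchanged treatment and on the source of any danger with the fact that the optimization method is assigned at random and repeated at scheduled visits.

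This is a wording amendment that uses the existing AE form and timelines. The downside is a modest number of extra non-serious AE forms, plus 24-hour notices for admissions that sites had been reading as non-serious.
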